**Figure 2 F2:**
[figure not shown]
The substantia nigra slice is placed to cover the midbrain with the highlighted voxels of interest for subsequent analyses highlighted in yellow in the sagittal (A) and axial planes (B). Placement of ^31^P-MRS slices. The basal ganglia slice is placed over the putamen aligned in both the coronal (C) axial planes (D), and voxels of interest for subsequent analyses are highlighted in yellow. One voxel covers the anterior putamen and another the posterior putamen.

Details of the acquisition sequences are shown in table 2. Spectra will be processed in the time domain using jMRUI software V.5.2 (http://www.jmrui.eu) and the Advanced Method for Accurate, Robust and Efficient Spectral fitting (AMARES) algorithm is used to determine the relative area under each peak.^33–35^ Analysis of the ^31^P-MRS data will focus on the change between randomisation and week 48 of normalised amplitudes of ATP, PCr and Pi, and ratio values such as PCr/ATP and Pi/ATP that assess bioenergetic dysfunction. All STH patients will undergo ^31^P-MRS. UCLH patients are also invited to attend the STH site for ^31^P-MRS.

**Table 2 T2:** Detailed parameters of the ^31^P protocol for acquisition

Sequence description	Localisation	Decoupling, NOE	TR (ms)	TE (ms)	NSA	Acquired voxel size (mm)	Reconstruction matrix	Reconstructed voxel size (mm)	Scan duration (min)
^31^P-Basal Ganglia	^31^P 2D CSI ISIS localisation	On	4000	0.22	10	40×40×20	12×12	17.5×17.5×20	12:48
^31^P-Substantia Nigra	^31^P 2D CSI ISIS localisation	On	4000	0.22	8	40×40×20	14×14	15×15×20	10:16

CSI, chemical shift imaging; ISIS, image-selected in vivo spectroscopy; NOE, nuclear overhauser efect; NSA, number of signal averages; TE, time to echo; TR, time to repetition.

### Gait analysis and activity monitoring

Physical activity and gait capacity will be assessed at two time points, namely prior to/during the baseline visit and prior to/during the week 48 visit at the end of the treatment period.

Physical activity will be assessed using home-based ‘real-life’ monitoring for seven consecutive days. A lightweight PAM containing a triaxial accelerometer, gyroscope, digital memory card and a battery (McRoberts, Dynaport Movemonitor+Netherlands) has been selected for continuous monitoring in all participants. Participants will wear the device for seven consecutive days and complete a diary to quantify their physical activity and gait characteristics within their normal weekly routine in a ‘real-world’ setting.

Gait capacity will be assessed during the study visits (figure 3) using a combination of wearable inertial sensors and an instrumented walkway. In particular, participants will complete gait analysis tasks during baseline and week 48 at the respective centre’s CRFs (STH and UCLH). Patients will complete three short gait tasks. First, participants will be asked to complete the 3 m timed up and go test walk at self-selected speed. It is an assessment of functional mobility that incorporates transitional actions of standing, turning and sitting.^36 37^ Then participants will complete two continuous gait tasks at self-selected preferred, and fast paced walking speeds. Each trial will consist of walking back and forth at least six times along the 8 m walkway with periods of quiet standing recorded at the start and end of each trial. At both sites, participants will wear the Dynaport Movemonitor+during instrumented gait tasks. At the Sheffield site, an instrumented 8 m walkway (OptoGait, Microgate Corporation, Bolzano, Italy) and a set of inertial sensors (Opals, APDM, Portland, Oregon, USA) will also be implemented. The instrumented walkway uses bar-mounted LEDs in a two dimensional configuration. The infrared signals transmitted are broken by the movement of the research subject’s feet during walking, and various spatiotemporal gait parameters such as step time, stride length, step width and stance time are computed. The system has a spatial resolution of 1 cm and a temporal resolution of milliseconds. The data from the inertial sensors will be used to monitor truncal sway during walking and provide a set of additional digitally mobility outcomes associated to the quality of gait (eg, gait smoothness, variability, symmetry, etc).^38 39^ The sensors will be positioned at both ankles, the lower back (L5), upper back (C7) and forehead. Each sensor contains an accelerometer, gyroscope and magnetometer and records synchronised data wirelessly. Data will be analysed with previously published, validated state of the art algorithms, implemented in Matlab.^38 40 41^

**Figure 3 F3:**
[figure not shown]
Protocols deployed at the two sites. all participants undergo 7-day physical activity monitoring in order to estimate physical activity levels and capture temporal and gait quality measures in a real-world setting. In-clinic instrumented gait tasks are also completed at both sites to provide spatiotemporal and gait quality measures of gait capacity. At UCL only red sensor location is implemented.

## Statistical analysis

These analyses will include all randomised patients (an intention-to-treat analysis population). The primary outcome of safety and tolerability will be reported using descriptive statistics and comparisons between treatment groups. Demographic and clinical assessment data will be summarised.

For each of the secondary outcomes, the change from baseline will be summarised within treatment groups using standard summary statistics (number of participants, mean, SD, median, minimum and maximum) with appropriate statistical tests assessing for significant differences depending on the distribution of the data and any relevant covariates.

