**Methods and analysis:**

This is a phase II, two-centre, double-blind, randomised, placebo-controlled trial of UDCA at a dose of 30 mg/kg in 30 participants with early PD. Treatment duration is 48 weeks, followed by an 8-week washout phase. Randomisation is 2:1, drug to placebo. Assessments are performed at baseline, week 12, 24, 36, 48 and 56. The primary outcome is safety and tolerability. Secondary outcomes will compare the change between baseline and week 48 using the following three approaches: the Movement Disorders Society Unified Parkinson’s Disease Rating Scale Part 3 in the practically defined ‘OFF’ medication state; confirmation of target engagement, applying ^31^Phosphorus MR Spectroscopy to assess the levels of ATP and relevant metabolites in the brain; and objective quantification of motor impairment, using a validated, motion sensor-based approach. The primary outcome will be reported using descriptive statistics and comparisons between treatment groups. For each secondary outcome, the change from baseline will be summarised within treatment groups using summary statistics and appropriate statistical tests assessing for significant differences. All outcomes will use an intention-to-treat analysis population.

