**Trial registration number:**

NCT03840005.

Strengths and limitations of this studyThis is the first double-blind, randomised, placebo-controlled trial of ursodeoxycholic acid (UDCA) in Parkinson’s disease (PD).This study uses novel secondary outcomes not previously used in a clinical trial studying PD; namely ^31^Phosphorus MR spectroscopy (^31^P-MRS) of disease-specific regions and detailed, complementary home and clinic-based motor activity and gait analysis.^31^P-MRS will allow the assessment of mitochondrial dysfunction directly in the midbrain, including the substantia nigra, the most severely affected brain area in PD.A limitation of the study is the considerable number of capsules patients will have to take; patients will on average be taking an additional nine extra capsules of medication each day through the trial, significantly increasing their ‘pill burden’.A further limitation is the small sample size of n=30 with 20 patients on UDCA and 10 patients on placebo, it will not be possible to draw firm conclusions about the neuroprotective effect of UDCA in PD but will allow for appropriate power and sample size calculations for future studies.

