### Primary outcome

The primary outcome for the UP study is to compare the safety and tolerability of UDCA at 30 mg/kg in PD compared with placebo as indicated by the following: the number of serious adverse events (SAEs), number of adverse treatment reactions and the number of patients completing the study. The safety and tolerability of UDCA in this study will be compared descriptively with the reported safety and tolerability of exenatide in the exenatide-PD trial, which followed a broadly similar trial design.^15^

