### Sample size

The primary outcome of interest for this study is the safety and tolerability of UDCA which will be assessed by comparing the rate of SAEs in the UDCA and placebo groups, alongside review of adverse treatment reactions and study completion. As the study is a pilot, it is not powered to compare the SAE rate between the groups statistically, but any SAEs in either group will be presented descriptively, the placebo group providing a baseline against which to view any SAEs in the UDCA group. Should this study result in no SAEs then it would be of interest to determine how likely it is that a larger study would find an intolerable rate of SAEs. For this purpose, we will consider the rate of SAEs reported in the exenatide PD trial to be tolerable and acceptable (ie, 20%).^15^ In this study, should no SAEs be found in the group receiving UDCA (n=20) then the likelihood that the true SAE rate is less than 20% is 0.990778.

The sample size has not been prospectively adjusted to account for any lost to follow-up. Instead, as the trial is of a relatively short duration we have instead allowed for any participants withdrawing from the study or lost to follow-up before the completion of 12 weeks of treatment to be replaced with a new participant.

The study has not been powered formally for the secondary or exploratory outcome measures, therefore, interpretation will concentrate on observed trends and confidence intervals for estimated differences. The data collected for the secondary and exploratory outcomes will allow the estimation of the effect size and variance in each outcome to facilitate formal power calculations for future phase III studies. Of note, there is currently no longitudinal clinical trial data using either ^31^P-MRS or our sensor-based approached quantification of motor impairment. The collection of such data is critical to allow high-quality future trial design using these novel outcome measures.

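### The primary adverse-event outcomes are assigned to all randomised patients, although the zero-SAE statement is worded for those receiving UDCA; a treated set would be the better denominator (minor)

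*Protocol article*

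**What the plan says.** The analysis population is stated in two places in the protocol article. The abstract (Methods and analysis) says: "All outcomes will use an intention-to-treat analysis population". The Statistical analysis section opens with "These analyses will include all randomised patients (an intention-to-treat analysis population", and its next sentence is "The primary outcome of safety and tolerability will be reported using descriptive statistics and comparisons between treatment groups". No safety set or as-treated set is named.

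The Primary outcome section defines safety and tolerability by "the number of serious adverse events (SAEs), number of adverse treatment reactions and the number of patients completing the study".

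The Sample size section says that safety will be assessed by comparing SAE rates between the arms, descriptively and without formal power. Its one quantitative safety statement is: "should no SAEs be found in the group receiving UDCA (n=20) then the likelihood that the true SAE rate is less than 20% is 0.990778". That section also allows participants who withdraw or are lost before completing 12 weeks of treatment to be replaced. It does not say how a replaced participant is counted.

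**The concern.** Two definitions of the safety denominator stand side by side. One rests on randomisation (abstract, Statistical analysis) and the other on exposure (Sample size). They give the same set only if every randomised participant takes the assigned treatment.

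For an efficacy comparison, keeping everyone as randomised protects against selection. For adverse events the argument runs the other way. A participant who never takes a capsule cannot have a drug reaction but still enlarges the denominator. An SAE in such a person would be a background event credited to the assigned arm. A participant given the other treatment would have any events counted under the wrong arm. Dilution makes the drug look slightly safer than it is among people who took it.

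This is a rule the article states, not a detail it leaves to a later document. A statistical analysis plan that set up a treated population would have to depart from the abstract's wording on all outcomes. Safety is also the trial's primary question, so the denominator should be settled before unblinding.

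**Working it through.** **Inputs**

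- Planned arms: 20 UDCA and 10 placebo, from 30 randomised 2:1 (strengths and limitations list; Design).
- Tolerable SAE rate: 20% (Sample size).
- Stated probability with no SAEs among 20: 0.990778 (Sample size).
- Number randomised but never dosed: not given. A range of 0 to 4 of the 20 UDCA participants is assumed for illustration.

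**Step 1: reproduce the stated figure.** With a uniform prior on the SAE rate and 0 events in n participants, the posterior probability that the rate is below 0.20 is 1 − 0.8^(n+1). For n=20 this is 1 − 0.8^21 = 0.990777, which agrees with 0.990778 apart from the last digit. The article does not name the prior; it is inferred from this match. The simpler form 1 − 0.8^20 gives 0.98847, which is not the stated figure.

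**Step 2: see which n the article used.** The n in "should no SAEs be found in the group receiving UDCA (n=20" equals the full planned UDCA arm, described elsewhere as "small sample size of n=30 with 20 patients on UDCA and 10 patients on placebo". The calculation thus treats assigned to UDCA and receiving UDCA as the same 20 people. The two definitions differ in wording, but no two numbers disagree.

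**Step 3: let m of 20 be dosed, without replacement.** The last column assumes that SAEs occur only in dosed participants, so the proportion on the randomised denominator is 0.20 × m/20.

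| Dosed, m | Zero SAEs: 1 − 0.8^(m+1) | A 20% rate in the dosed, shown over all 20 |
|---|---|---|
| 20 | 0.9908 | 20% |
| 19 | 0.9885 | 19% |
| 18 | 0.9856 | 18% |
| 17 | 0.9820 | 17% |
| 16 | 0.9775 | 16% |

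Each undosed participant lowers the observed proportion by 1/20, or 5% in relative terms. The zero-SAE probability stays above 0.97 throughout.

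**Step 4: two undosed UDCA participants who are replaced (assumption).** Then 22 are randomised and 20 are dosed.

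- Zero SAEs: n=20 gives 0.9908. Using the randomised count of 22 gives 1 − 0.8^23 = 0.9941, with no added exposure.
- Three participants with an SAE, all dosed: 3/20 = 15.0% (Clopper-Pearson 95% interval 3.2% to 37.9%) against 3/22 = 13.6% (2.9% to 34.9%).

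**Step 5: dosed participants who are replaced.** If the two early leavers had taken capsules, all 22 would belong in a treated set, and n=22 would be the right count. A total above 20 is therefore not in itself a fault. Only undosed participants separate the two sets in number; wrong-treatment cases change the arm and not the total.

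**The case against.** Much of the case against making more of this stands.

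- **Self-contradiction in the numbers.** A reader might infer that the stated 0.990778 is wrong or inflated. It is not: it reproduces at n=20, the planned UDCA arm, and the Sample size wording already conditions on receipt of UDCA. Nothing there tells the analyst to substitute a larger randomised count.
- **Replacement as the source of dilution.** A reader might infer that replacement inflates the safety denominator. The rule concerns people leaving before 12 weeks of treatment are complete, most of whom will have started treatment. They were exposed and belong in any safety set. Keeping them is protective, because their events and non-completion remain visible.
- **Undosed participants are hypothetical.** Table 1 places randomisation and first medication supply at the same baseline visit. Supply does not prove ingestion, but the two sets should coincide or nearly so. Nothing in the article suggests wrong-treatment cases.
- **Counts are not diluted.** The primary outcome is mainly a set of numbers of events and patients, and no test or decision rule depends on the denominator. This stands only in part, because the Sample size section speaks of comparing SAE rates and sets 20% as the tolerable level.
- **One capsule is little exposure.** Treatment starts at one capsule a day and is increased stepwise, so a treated set still includes people with very little drug. That is true, but such people can at least have a reaction.
- **The full protocol or the analysis plan may define a safety set.** That is possible, but the abstract's sentence on all outcomes would then need correcting.

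For study completion, the third component of the primary outcome, all randomised is the right denominator and should stay.

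**Conclusion.** The point holds as a minor one. The article fixes an all-randomised, as-assigned population for SAEs and adverse treatment reactions, and a treated set analysed by treatment received suits those outcomes better. The effect is nil if everyone takes the assigned treatment. With 18 of 20 dosed and no SAEs, the probability is 0.9856 rather than 0.9908. With two undosed and replaced participants, a 15.0% SAE proportion would show as 13.6%, a shift of 1.4 percentage points against intervals more than 30 points wide. None of these shifts changes the conclusion.

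These sizes rest on assumed numbers of undosed participants and on the uniform prior inferred from the stated figure. The documents do not support the stronger claim that the primary safety result is materially biased in favour of UDCA: they give no undosed count, and the planned n and the stated probability agree with each other.

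**What to change.** Change the population sentence in the abstract and in the Statistical analysis section, before unblinding, so that it says the following:

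- SAEs and adverse treatment reactions are summarised in participants who took at least one capsule, by treatment actually received. Dosed participants who withdrew early and were later replaced are included.
- Study completion and the secondary outcomes are analysed in all randomised participants, including those replaced.

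In the Sample size section, add that the zero-SAE calculation will use the actual number of participants who took UDCA as n, whether that is below or above 20.

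The cost is a sentence or two. The safety set may be smaller than the randomised set by a few participants; report their number by arm, together with any participant analysed under a treatment other than the one assigned. Returned medication is already counted to assess compliance, so little new data collection should be needed.

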## Data management

Data will be kept in accordance with Good Clinical Practice, the Data Protection Act 2018 and General Data Protection Regulations. Data management will be provided by the University of Sheffield CTRU. All data will be entered remotely on to a centralised database held within the CTRU (Prospect) by a research study member at the study site. Access to Prospect is controlled by usernames and encrypted passwords.

All participants will be assigned a unique participant ID number at screening that will link all of the clinical information held about them on the study database. It will also be used in all correspondence between CTRU and participating centres.

## Ethics and dissemination

This trial has been approved by the East of England – Cambridgeshire and Hertford Shire Research Ethics committee (Protocol ID: 18/EE/0280) in November 2018. The study will be conducted in accordance with the local R&D approval and the Declaration of Helsinki. All participants provide written informed consent prior to any study procedures commencing. The results will be published in a peer-reviewed journal and presented at regional, national and international scientific meetings as appropriate. A plain English summary of the study results will be sent to the study participants once data analysis has been completed. Results of the study may also be presented at meetings of PD support groups or to other relevant lay audiences.

## Discussion

We propose a novel study design for early, proof of concept PD neuroprotection trials, combining assessment for safety and tolerability with ^31^P-MRS-based assessment of target engagement of bioenergetics pathways and motion sensor-based objective quantification of disease progression. Our study protocol will be particularly powerful for any compound aiming to directly improve mitochondrial function in PD. Additionally, our approach of using ^31^P-MRS also holds promise to determine biologically relevant target engagement for compounds aiming at genetically defined upstream targets such as antisense oligonucleotides for *LRRK2* or antibody therapy for alpha-synuclein. Mitochondrial dysfunction is a well-recognised aspect of both LRRK2- and alpha-synuclein-associated PD.^42 43^

A recent open-label study of UDCA over 6 weeks with an escalating dose up to 50 mg/kg in five patients with mild to moderate PD found reasonable tolerability and also used ^31^P-MRS to assess target engagement.^44^ However, their ^31^P-MRS imaging data were obtained in only three participants and their methodology differed in that a surface coil was used and to acquire occipital lobe spectra only.

In-depth sensor-based gait analysis has the potential to overcome the current limitations of the MDS-UPDRS-based clinical assessment.^18^ Gait analysis provides a method of quantifying gait disability and postural instability and therefore has potential as an objective motor endpoint for future studies. There is clear evidence that greater axial involvement predicts a poorer outcome in PD with regard to both cognitive decline and postural instability.^23^ It is, therefore, likely that the greatest value in sensor-based analysis is in assessing a combination of spatiotemporal and upper body gait characteristics both in the formal clinical setting but also in exploring real-life mobility through at-home monitoring.^38 45 46^

UDCA has previously been trialled in another neurodegenerative disorder, MND at doses of 15, 30 and 50 mg/kg in a total of 18 patients. Patients were treated for 4 weeks. The main AEs were minor gastrointestinal side effects, graded as mild to moderate. Side effect profiles and frequency were broadly similar between groups without a clear dose correlation.^13^ This represents grounds to hypothesise that the primary outcome of safety and tolerability of UDCA at 30 mg/kg in PD will be achievable. We expect completion of the study analysis by July 2021.
